## Abstract

**Background:**

Degenerative aortic valve disease accounts for 10–20% of all cardiac surgical procedures. The impact of pre-existing comorbidities on the outcome of patients undergoing surgical aortic valve replacement (SAVR) needs further research.

**Methods:**

The IMPACT registry is a non-interventional, prospective, open-label, multicenter, international registry with a follow-up of 5 years to assess the impact of pre-existing comorbidities of patients undergoing SAVR with the INSPIRIS RESILIA aortic valve on outcomes. IMPACT will be conducted across 25 sites in Austria, Germany, The Netherlands and Switzerland and intends to enroll approximately 500 patients. Patients will be included if they are at least 18 years of age and are scheduled to undergo SAVR with the INSPIRIS RESILIA Aortic Valve with or without concomitant ascending aortic root replacement and/or coronary bypass surgery. The primary objective is to determine all-cause mortality at 1, 3, and 5 years post SAVR. Secondary objectives include cardiac-related and valve-related mortality and structural valve deterioration including hemodynamics and durability, valve performance and further clinical outcomes in the overall study population and in specific patient subgroups characterized by the presence of chronic kidney disease, hypertension, metabolic syndrome and/or chronic inflammation.

**Discussion:**

IMPACT is a prospective, multicenter European registry, which will provide much-needed data on the impact of pre-existing comorbidities on patient outcomes and prosthetic valve performance, and in particular the performance of the INSPIRIS RESILIA, in a real-world setting. The findings of this study may help to support and expand appropriate patient selection for treatment with bioprostheses.

**Trial registration:**

ClinicalTrials.gov identifier: NCT04053088.

## Background

Degenerative aortic valve disease (DAVD) is a condition that leads to deterioration of the heart valves and is an emerging health problem with broad consequences for the patient and the healthcare system alike [1]. Treatment for DAVD is either transcatheter aortic valve implantation (TAVI) or surgical aortic valve replacement (SAVR) with either mechanical or bioprosthetic valves [2].

Within this context, it is known that risk factors, like diabetes, low-density lipoprotein (LDL) cholesterol, hypertension and smoking, increase the likelihood of developing DAVD [3]. It is also clear that some treatments, like SAVR or TAVI, confer risk for direct postoperative complications, such as the development of acute kidney injury, which may affect patient survival [4, 5]. But the impact of pre-existing comorbidities on the outcome of patients undergoing SAVR is less clear. Not only are comorbidities associated with surgical complications, but they also impact on the quality of the patient’s recovery and their long-term functional recovery after surgery [6]. A study to determine the impact of comorbid illness on mortality outcomes after cardiac surgery has shown that diabetes, vascular disease, chronic obstructive pulmonary disease (COPD), peptic ulcer disease and renal failure significantly increase the risk of death after coronary artery bypass grafting (CABG) [7]. Another recent study has shown that comorbidity, as measured by the Charleston comorbidity index (CCI), is an independent risk factor for both 1- and 3-year mortality in patients undergoing SAVR [8]. While more work is needed to establish which comorbidities will impact on the outcome of SAVR, there are certain known comorbidities that are very likely to have a negative impact on the outcome of SAVR – these include renal dysfunction, pulmonary hypertension and diabetes [9–11]. Thourani et al conducted a large-scale study to determine the impact of renal dysfunction – ranging from mild renal dysfunction (glomerular filtration rate [GFR] 60–90 mL/min) to severe renal dysfunction (GFR 15–30 mL/min) – on SAVR and concluded that the presence of pre-existing renal dysfunction is associated with poor prognosis. Furthermore, the more severe the renal dysfunction, the worse the outcome post-SAVR [10]. The impact of diabetes, however, warrants further investigation. Diabetes is typically associated with worse outcomes after surgery [11, 12]. Surprisingly, however, a study of patients with and without type 2 diabetes mellitus (T2DM) undergoing either TAVI or SAVR suggested that the prognosis of patients with T2DM was not different to non-diabetic patients [13].

While mechanical valves have been the mainstay of SAVR, the use of bioprostheses for the surgical treatment of valve diseases has increased considerably over the last decade [14]. They were introduced to improve the hemodynamic performance of the valves and to reduce the risk of structural valve deterioration (SVD) [15]. This was accompanied by improvements of tissue preservation technologies, which resulted in a reduction of intracellular calcium infiltration, stiffening and weakening of the tissues. There is, however, still a lack of data on the impact of patients’ predisposing risk factors such as chronic kidney disease (CKD) [16] diabetes and the metabolic syndrome (MS) [17] and age. However, literature on this topic is scattered and data are scarce.

Bioprosthetic valve durability cannot, therefore, be generalized as it is influenced by the type and design of the implanted prosthetic valve, and the particular physiology of the patient. To better understand the impact of pre-existing comorbidities on the outcome of SAVR using bioprosthetic valves, we developed a multicenter registry to gather long-term follow-up data on patients implanted with the INSPIRIS RESILIA aortic valve concerning SVD and valve performance, with a particular focus on patients with pre-existing chronic kidney disease, diabetes, hypertension, metabolic syndrome or chronic inflammation. Information from this study will enable clinicians to make informed decisions regarding the use of SAVR in comorbid patients.

## Methods/design

The IMPACT registry is a non-interventional, prospective, open-label, multicenter, international registry with a follow-up of 5 years to assess the impact of pre-existing comorbidities on outcomes of patients undergoing surgical aortic valve replacement (SAVR) with the INSPIRIS RESILIA aortic valve (Edwards Lifesciences). An estimated 500 patients will be enrolled across 25 sites in Germany, Austria, the Netherlands and Switzerland, with a mean of 20 patients per site enrolled over a 12-month period. Site selection is based on recommendations of the steering committee and on the site’s prior SAVR experience. The registry will be conducted in accordance with the European Medical Device Regulation (Regulation (EU) 2017/745 of 5 April 2017) and ISO 14155:2011. Patients will need to provide written, informed consent prior to enrolment.

### The valve

The INSPIRIS RESILIA aortic valve, is a stented trileaflet valve comprised of RESILIA bovine pericardial tissue that is mounted on a flexible frame. The valve is stored under dry packaging conditions and consequently does not require rinsing prior to implantation. RESILIA tissue is the result of a technology that incorporates a stable-capping anticalcification process permanently blocking residual aldehyde groups that are known to bind with calcium. It also includes tissue preservation with glycerol, which replaces the traditional storage in liquid-based solutions such as glutaraldehyde. As such leaflet calcification and hemodynamic performance is improved [18]. The frame is designed to be compliant at the orifice as well as at the commissures. The wireform is made of a corrosion-resistant cobalt-chromium alloy to improve spring efficiency and fatigue-resistance and is covered with a polyester fabric. Finally, VFit technology, which includes fluoroscopically visible size markers and an expansion zone, eases potential future valve-in-valve (ViV) procedures.

### Patients

Patients over the age of 18 years undergoing SAVR and receiving the INSPIRIS RESILIA Aortic Valve will be enrolled on a consecutive basis. In addition to the applicable criteria of the device Instructions for Use (IFU), the registry inclusion criteria stipulate that patients have an aortic valve vitium and require aortic valve replacement, and are scheduled to undergo SAVR using the INSPIRIS RESILIA aortic valve with or without concomitant ascending aortic root replacement and/or coronary bypass surgery. Patients are scheduled to attend yearly follow-up visits on site for up to five years.

Patients will be excluded if they have active endocarditis or myocarditis, or had endocarditis or myocarditis within three months prior to the scheduled SAVR, if valve implantation is not possible in accordance with the device IFU, the patient has a life expectancy of less than 12 months for any reason, or the patient is pregnant at the time of the surgery.

### Objectives

The primary objective of the study is to determine all-cause mortality at 1, 3, and 5 years after SAVR (Table 1). The secondary objectives are designed to assess the study population mortality, hemodynamics and durability of the prosthetic valve, and clinical outcomes. Study population mortality is defined as all-cause, cardiac- and valve-related mortality in the overall study population and in the following patient subgroups at all time points: patients with chronic kidney disease, diabetes, hypertension, metabolic syndrome and chronic inflammation. Assessment of hemodynamics and durability will include the hemodynamic performance of the INSPIRIS RESILIA aortic valve in the overall study population and stratified according to the different patient subgroups including patient prosthesis mismatch (PPM) including maximum (Pmax) and mean (Pmean) pressure gradient across the valve, velocity time integral (VTI), prosthesis opening area (EOA), left ventricular ejection fraction (LVEF) and paravalvular leak (PVL); severe hemodynamic SVD following Salaun [19]; and potential valve-in-valve (ViV) procedures and clinical outcome including follow-up. Clinical outcomes will be assessed in the overall study population and, in addition, will be stratified across the following patient subgroups: New York Heart Association (NYHA) functional class compared to baseline, freedom from valve-related rehospitalization, new pacemaker implant and freedom from valve-related complications. Exploratory safety endpoints are presented in Table 1.

**Table 1 Tab1:** Registry objectives

Primary objectives	To determine all-cause mortality 1, 3, and 5 years after surgery
**Secondary objectives**	**Mortality**
	To determine all-cause, cardiac- and valve-related mortality in the overall study population and in different patient subgroups at all timepoints:
	• Chronic kidney disease
	• Diabetes
	• Hypertension
	• Metabolic syndrome
	• Chronic inflammation

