### Data collection

The clinical outcome data collected will be based on the site’s standards of care for SAVR. The collected data will include medical history, physical assessments, safety parameters, electrocardiogram (ECG), laboratory results and transthoracic/transesophageal echocardiography (Table 2). Data will be captured by an electronic case report form (eCRF; Software for Trials Europe GmbH, Berlin, Germany) and data will be checked automatically for plausibility and completeness.

**Table 2 Tab2:** Data collection schedule

	Screening/baseline	Surgery	Discharge	Year 1	Year 3	Year 5
Medical history^1^	X					
Physical examination^2^	X		X	X	X	X
ECG (12-lead)	X		X	X	X	X
Echocardiogram (TTE)	X		X	X	X	X
Core Lab echo				X		X
NYHA class/CCS angina class	X			X	X	X
Medications	X		X	X	X	X
Procedural information		X				
Aetiology		X				
SAE reporting		X	X	X	X	X
Discharge data			X			
Rehospitalization data^3^				X	X	X
Return to work				X	X	X

^1^Includes cardiovascular and non-cardiovascular conditions, prior cardiac interventions and surgeries

^2^Physical examination, includes height, weight and vital signs (blood pressure and heart rate)

^3^Includes re-interventions, potential ViV procedures

*Legend:* CCS, Canadian Cardiovascular Society; ECG, electrocardiogram; NYHA, New York Heart Association; SAE, serious adverse event(s); TTE, transthoracic echocardiogram

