### Statistical analysis

The study sample size was determined based on feasibility considerations. Furthermore, 95% confidence intervals (CIs) for the primary endpoint at different event rates were determined and taken as a basis for the final sample size. It was estimated, from the COMMENCE Trial dataset where all-cause mortality was determined to be 1.2% at year 1 and 2.0% at year 2 [20], that 500 patients will arrive at a 95% confidence interval (CI) of ±0.87 for a 1% observed event rate and ± 1.50 for a 3% observed event rate.

Statistical analyses will be performed for the total study population and for the subgroups defined by baseline comorbidities if applicable. Continuous variables will be presented as mean ± standard deviation (SD) or as median with interquartile range (IQR), and categorical variables (e.g., gender) will be reported as frequencies and percentages. The Kolmogorov-Smirnov test will be used to test for normal distribution. Accordingly, comparisons will be performed using Student’s t-test or Mann-Whitney U test for continuous variables. The Chi-Square or Fisher exact test will be used for categorical variables. Linearized rates and actuarial probability statistics may be used where appropriate for adverse event reporting. Kaplan-Meier analyses will be performed for survival and safety outcomes. All statistical analyses will be performed using IBM SPSS Statistics version 24 (IBM, Armonk, New York) or R Core Team (https://www.R-project.org/), with a *p*-value of < 0.05 considered statistically significant.

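### Valve gradients, EOA and LVEF are set against comorbidity with unadjusted tests only, so differences in implanted valve size or pre-operative LVEF could be read as comorbidity effects

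*Protocol article*

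**What the plan says.** All references are to the protocol article.

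- **Objectives and Table 1.** A secondary objective covers "hemodynamic performance of the INSPIRIS RESILIA aortic valve in the overall study population and stratified according to the different patient subgroups". The measures listed are PPM, maximum and mean gradient, VTI, EOA, LVEF and paravalvular leak. NYHA class is to be compared with baseline; nothing similar is said of LVEF.
- **Statistical analysis.** "Statistical analyses will be performed for the total study population and for the subgroups defined by baseline comorbidities if applicable". For continuous variables, "comparisons will be performed using Student’s t-test or Mann-Whitney U test for continuous variables". For the rest, "The Chi-Square or Fisher exact test will be used for categorical variables". Kaplan-Meier analysis is named for survival and safety outcomes. The threshold is a p-value "of < 0.05 considered statistically significant". No regression, covariate or valve-size stratum is named for any outcome.
- **Discussion, Comorbidities.** The stated need is to find out whether pre-existing comorbidities affect patient outcomes or the performance of the prosthesis, and if so which ones.
- **Data collection, Table 2.** A transthoracic echocardiogram is scheduled at baseline, discharge and years 1, 3 and 5. Height and weight are part of the physical examination at the same visits. Procedural information is recorded at surgery. Valve size is not named as an item.

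**The concern.** Gradient and EOA depend on the size of the valve that was implanted. All patients receive the same model, but a single model does not mean a single size: the section on the valve mentions size markers. If one comorbidity group received more small valves, its gradients would be higher and its EOA lower even if the comorbidity did nothing to the prosthesis.

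LVEF raises a similar problem. It is listed among the measures of valve performance, yet its follow-up value partly carries forward the pre-operative value. A group that enters surgery with poorer ventricular function will probably show a lower LVEF later, whatever the valve does.

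A t-test, Mann-Whitney, Chi-square or Fisher test cannot take account of either factor. At stake is the interpretation of a named secondary objective whose results are meant to inform patient selection.

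**Working it through.** **The plan's own figure.** The only precision statement concerns mortality with 500 patients. The half-width 1.96 × √(p(1−p)/500) gives 0.87 points at p = 1% and 1.50 points at p = 3%, as stated. No figure is given for the hemodynamic comparisons, so nothing in the plan bounds the problem.

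**Illustration.** From the plan: 500 patients and the 0.05 threshold, taken as two-sided. Everything else is assumed: all patients evaluable, no true comorbidity effect, and a subgroup share of 20%, so groups of 100 and 400. With d the difference produced by imbalance alone and SE = SD × √(1/100 + 1/400) = SD × 0.1118, the chance of p<0.05 is Φ(d/SE − 1.96) + Φ(−d/SE − 1.96).

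*Mean gradient.* Assumed: EOA 1.4 against 1.7 cm² for two adjacent sizes; gradient varying with 1/EOA² at equal flow; mean gradient 10 mmHg with the larger valve; SD 4 to 5 mmHg. The gradient ratio is (1.7/1.4)² = 1.474, so the smaller valve adds 4.74 mmHg. SE = 0.447 (SD 4) or 0.559 (SD 5).

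| Excess of small valves in one group | d (mmHg) | d/SE, SD 5 to SD 4 | Chance of p<0.05 |
|---|---|---|---|
| 5 points | 0.05 × 4.74 = 0.24 | 0.42 to 0.53 | 7% to 8% |
| 10 points | 0.10 × 4.74 = 0.47 | 0.85 to 1.06 | 14% to 19% |
| 20 points | 0.20 × 4.74 = 0.95 | 1.70 to 2.12 | 40% to 56% |

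The subgroup share matters too. For a gap of 1.0 mmHg at SD 5, the chance is 27%, 43% or 54% at shares of 10%, 20% or 30%.

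*LVEF.* Assumed: SD 10 points, baseline gap D of 3 to 5 points, correlation ρ of baseline with follow-up 0.5 to 0.7, equal SDs at both times. The carried-over gap is ρ × D and SE = 1.118.

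| ρ | D | ρ × D | d/SE | Chance of p<0.05 |
|---|---|---|---|---|
| 0.5 | 3 | 1.5 | 1.34 | 27% |
| 0.6 | 3 | 1.8 | 1.61 | 36% |
| 0.6 | 5 | 3.0 | 2.68 | 77% |
| 0.7 | 5 | 3.5 | 3.13 | 88% |

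At a share of 10% the range is 17% to 65%; at 30% it is 34% to 95%.

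The result is driven by the assumed imbalance. With a small one the error rate stays close to 5%; with a moderate one it does not.

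**The case against.** **Covariates and table layouts belong in the analysis plan.** This is largely right: an article need not list them, and their absence alone would be no finding. What stands is that the article does fix the family of comparisons and the threshold. An analysis plan that follows it gives unadjusted tests; one that adjusts departs from it.

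**Stratified may mean descriptive.** No sentence ties the t-test to gradient, EOA or LVEF by comorbidity, and the subgroup analyses are to be done only where applicable. That reading is possible. But the Discussion states an aim about impact, and no other method is named that could serve it for these measures. If description is all that is meant, the plan should say so.

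**Serial echocardiograms on the same patient are planned.** Change within a patient is less exposed to valve-size mix, since the size stays constant unless the valve is replaced. However, core-lab reading covers years 1 and 5 only. It supplies neither a baseline LVEF nor a comparison between groups that takes account of size.

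**Adjustment is not neutral.** This stands. Lower baseline LVEF may itself follow from the comorbidity, and body size may be part of metabolic syndrome, so adjusted and unadjusted estimates answer different questions. In groups that differ at baseline, covariance analysis and change from baseline can also disagree.

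**Two stronger readings are tempting.** A reader might infer that the objective will be answered wrongly. The documents do not support that: they show neither an imbalance nor its direction for any comorbidity. A reader might also infer that body size is ignored. It is not: PPM, as usually understood, relates valve area to body size and is a listed outcome, and height and weight are collected. That its formula is not given is ordinary omitted detail in an article.

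**Conclusion.** The point holds in limited form. The stated tests cannot separate comorbidity from valve-size mix or pre-operative LVEF, while the stated aim is to learn whether comorbidity affects valve performance. Differences of either kind could therefore be misattributed.

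By how much cannot be derived from the documents. The percentages shown rest on assumed orifice areas, SDs, correlations, subgroup shares and imbalances. They show that the risk runs from negligible to serious within plausible inputs, not that it will materialise. The point concerns secondary objectives; the primary objective, all-cause mortality, is unaffected.

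**What to change.** In the Statistical analysis section, state that:

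1. gradients and EOA are tabulated by labelled valve size and compared between comorbidity groups by regression that includes valve size;
2. follow-up LVEF is compared between groups with baseline LVEF as covariate;
3. unadjusted results are shown alongside, so that both questions can be read;
4. for metabolic syndrome, body-size-adjusted results are a sensitivity analysis only, because body size may be part of the condition.

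If this is not wanted, label the subgroup hemodynamic results as descriptive and draw no conclusion from them about the effect of comorbidity on the valve.

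The cost is wording and slightly more analysis work. Baseline echocardiography, height and weight are already scheduled. Labelled valve size presumably falls under procedural information, but Table 2 does not name it, so the case report form should be checked. The downside is interpretive: where baseline LVEF is a consequence of the comorbidity, the adjusted estimate answers a conditional question, and the report should say so.

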	**Hemodynamic performance and durability**
	• Hemodynamic performance of the INSPIRIS RESILIA Aortic Valve™ in the overall study population and stratified according to the different patient subgroups including patient prosthesis mismatch (PPM) including maximum (Pmax) and mean (Pmean) pressure gradient across the valve, Velocity Time Integral (VTI), Prosthesis Opening Area (EOA), Left Ventricular ejection fraction (LVEF), Paravalvular Leak
	• Severe hemodynamic structural valve deterioration (SVD) following Salaun [19]
	• Description of potential ViV procedures* and clinical outcome including follow-up
	**Clinical outcomes** (overall study population and stratified according to the different patient subgroups)
	• NYHA functional class compared to baseline
	• Freedom from valve-related rehospitalization
	• New pacemaker implantation
	• Freedom from valve-related complications
**Exploratory endpoints**	**Safety (defined according to VARC-2)**
	• SVD
	• Non-structural valve deterioration
	• Thromboembolic events (e.g., stroke)
	• Valve thrombosis
	• All bleeding/hemorrhage
	• Major bleeding/hemorrhage
	• All paravalvular leakage
	• Endocarditis
	• All-cause mortality
	• Cardiac-related mortality
	• Valve-related mortality
	• Re-intervention
	• Conduction disturbances

*Legend:* NYHA, New York Heart Association; SVD, structural valve degeneration; VARC, Valve Academic Research Consortium; ViV, valve-in-valve. *Valve-in-valve procedures include both transcatheter aortic valve implantations (TAVI) in surgical aortic valve replacements (SAVR) and SAVR in SAVR replacements

### Data collection

The clinical outcome data collected will be based on the site’s standards of care for SAVR. The collected data will include medical history, physical assessments, safety parameters, electrocardiogram (ECG), laboratory results and transthoracic/transesophageal echocardiography (Table 2). Data will be captured by an electronic case report form (eCRF; Software for Trials Europe GmbH, Berlin, Germany) and data will be checked automatically for plausibility and completeness.

**Table 2 Tab2:** Data collection schedule

	Screening/baseline	Surgery	Discharge	Year 1	Year 3	Year 5
Medical history^1^	X					
Physical examination^2^	X		X	X	X	X
ECG (12-lead)	X		X	X	X	X
Echocardiogram (TTE)	X		X	X	X	X
Core Lab echo				X		X
NYHA class/CCS angina class	X			X	X	X
Medications	X		X	X	X	X
Procedural information		X				
Aetiology		X				
SAE reporting		X	X	X	X	X
Discharge data			X			
Rehospitalization data^3^				X	X	X
Return to work				X	X	X

^1^Includes cardiovascular and non-cardiovascular conditions, prior cardiac interventions and surgeries

^2^Physical examination, includes height, weight and vital signs (blood pressure and heart rate)

^3^Includes re-interventions, potential ViV procedures

*Legend:* CCS, Canadian Cardiovascular Society; ECG, electrocardiogram; NYHA, New York Heart Association; SAE, serious adverse event(s); TTE, transthoracic echocardiogram

